## **8.2. Safety and other assessments**

### **Vital signs**

Vital signs include body temperature, respiration, pulse, and blood pressure. It is recommended to rest quietly for at least 3 minutes before measurement and to measure while sitting with the elbow at the same level as the heart. This should be done during the screening period, at the CnD28, EOT visits, and at the visit 28 days after the last medication.

### **Physical examination**

Physical examination includes skin and mucous membranes, lymph nodes, head and neck, chest, abdomen, spine, musculoskeletal system, nervous system, and other areas. It is conducted during the screening period, CnD28, end of treatment visit, and 28 days after the last dose of medication.

### **12-lead ECG**

The investigator should record the results of heart rate, QT, QTcF, QRS, and P-R interval, as well as clinically significant electrocardiogram abnormalities. QTcF is calculated using the following formula:  $QTcF = QT / (60 / HR)^{0.33}$ . Signed original electrocardiograms/copies will be archived at the study site. This will be done during the screening period, C1D15, CnD28, EOT visit, and 28-day follow-up after the last dose.

### **Echocardiography**

The investigator should record the left ventricular ejection fraction and abnormal results of echocardiography. This should be done during the screening period and end-of-treatment visit. If the patient has previously undergone an echocardiogram at the hospital and the examination

time meets the protocol requirements, the patient does not need to undergo the examination again. The results before signing the informed consent form should be used to determine the inclusion/exclusion criteria.

### Laboratory tests

Serology will be performed during the screening period, coagulation function and pregnancy tests will be performed during the screening period and at the end of treatment visit (EOT). Hematology, urinalysis, and blood biochemistry will be performed during the screening period, on Day 28 of Cycle 1, at EOT, and 28 days after the last dose of the study drug. If a patient has previously undergone relevant laboratory tests at the study site and the test results meet the protocol requirements, the patient does not need to undergo the tests again and the results prior to signing the informed consent form will be used to determine eligibility. Please refer to Table 8-1 for specific parameters of each test.

**Table 8-1 Laboratory Parameters**

|                                                                                                                                                                                                      |                                           |
|------------------------------------------------------------------------------------------------------------------------------------------------------------------------------------------------------|-------------------------------------------|
| Hematology                                                                                                                                                                                    | Gamma-glutamyl transferase (GGT)          |
| White blood cell count                                                                                                                                                                               | Creatinine                                |
| Red blood cell count                                                                                                                                                                                 | Urea/Urea Nitrogen                        |
| Hemoglobin                                                                                                                                                                                           | Uric acid                                 |
| Platelet count                                                                                                                                                                                       | Blood glucose (fasting)                   |
| Absolute Lymphocytes                                                                                                                                                                                 | Triglycerides                             |
| Absolute neutrophil count                                                                                                                                                                            | Total cholesterol                         |
| Monocyte count                                                                                                                                                                                       | Potassium                                 |
| Eosinophil count                                                                                                                                                                                     | Sodium                                    |
| Basophil count                                                                                                                                                                                       | Chlorine                                  |
| Urinalysis                                                                                                                                                                                    | Calcium                                   |
| Leukocytes                                                                                                                                                                                           | Coagulation                        |
| Urine occult blood                                                                                                                                                                                   | Plasma prothrombin time (PT)              |
| Urobilinogen                                                                                                                                                                                         | Activated partial prothrombin time (APTT) |
| Ketones                                                                                                                                                                                              | International normalized ratio (INR)      |
| Glucose (urine glucose)                                                                                                                                                                              | Pregnancy test                     |
| Erythrocyte quantitation                                                                                                                                                                             | Serum/Urine $\beta$ -HCG                  |
| Leukocyte quantitation                                                                                                                                                                               | Serum virology                     |
| Urine protein                                                                                                                                                                                        | Hepatitis B surface antigen (HBsAg)       |
| 24-hour urine protein quantification (to be tested when screening urine protein is $\geq++$ , and testing during treatment and follow-up period can be considered based on actual situation). | Hepatitis B surface antibody              |

|                                                                                                                                              |                                                    |
|----------------------------------------------------------------------------------------------------------------------------------------------|----------------------------------------------------|
| Blood chemistry                                                                                                                       | Hepatitis B e antigen                              |
| Total bilirubin (TBIL)                                                                                                                       | Hepatitis B e antibody                             |
| Direct bilirubin                                                                                                                             | Hepatitis B core antibody                          |
| Alanine aminotransferase (ALT)                                                                                                               | Hepatitis C antibody (Anti-HCV)                    |
| Aspartate aminotransferase (AST)                                                                                                             | Human immunodeficiency virus antibodies (Anti-HIV) |
| Albumin (ALB)                                                                                                                                | Hepatitis B virus DNA quantitation (HBV-DNA) *     |
| Alkaline phosphatase (ALP)                                                                                                                   | Hepatitis C virus RNA quantitation (HCV-RNA) *     |
| Lactate dehydrogenase (LDH)                                                                                                                  |                                                    |
| * HBV-DNA quantification should be tested when HBsAg is positive, and HCV-RNA quantification should be tested when HCV antibody is positive. |                                                    |

### 8.3. Adverse Events and Serious Adverse Events

#### 8.3.1. Definition

##### 8.3.1.1. Adverse Event (AE)

All adverse medical events that occur in patients after receiving the study drug may manifest as symptoms, signs, diseases, or laboratory abnormalities, but may not necessarily be causally related to the study drug.

##### 8.3.1.2. Adverse Drug Reaction (ADR)

Any harmful or unexpected reaction related to the study drug that may occur during a clinical study. There is at least a reasonable possibility of a causal relationship between the study drug and the AE, which cannot be ruled out.

##### 8.3.1.3. Treatment-Emergent Adverse Events (TEAEs)

Events that occur during treatment that are not present before treatment or have worsened compared to before treatment.

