## 1.2. Schedule of Assessment

| Test Period                                                            | Screening |       | Treatment Period |          |          | End of
Treatment/Withdrawal Visit
(EOT) [3] | Safety Follow-up Period    | Follow-
up     |
|------------------------------------------------------------------------|-----------|-------|------------------|----------|----------|---------------------------------------------------|----------------------------|-------------------|
| Visit time                                                             | -28~-1    | -7~-1 | C1D1             | C1D15[1] | CnD28[2] | Within 14 days of the last
dose                | Day 28 after the last dose | Every 12
weeks |
| Window                                                                 | N/A       | N/A   | N/A              | ± 1 day  | ± 3 days | N/A                                               | ± 3 days                   | ± 7 days          |
| Informed Consent                                                       | ×         |       |                  |          |          |                                                   |                            |                   |
| Demographic data [4]                                                   | ×         |       |                  |          |          |                                                   |                            |                   |
| Height/Weight [5]                                                      | ×         |       |                  |          | ×        | ×                                                 |                            |                   |
| Tumor History and Treatment
History [6]                             | ×         |       |                  |          |          |                                                   |                            |                   |
| Tumor tissue samples or blood
collection [7]                        | ×         |       |                  |          |          |                                                   |                            |                   |
| Personal and other past medical
history or concomitant diseases [8] | ×         |       |                  |          |          |                                                   |                            |                   |

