#### **Secondary endpoints:**

- ORR evaluated by the investigator according to RECIST 1.1 criteria.
- The disease control rate (DCR), progression-free survival (PFS), and duration of response (DOR) were evaluated by both the investigator and an independent review committee according to the RECIST 1.1 criteria.
- Overall survival (OS);
- Treatment-emergent adverse events (TEAEs) and serious adverse events (SAEs) during the treatment period.
- Plasma concentrations of HA121-28.

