### **8.3.7. Collection, Recording and Evaluation of Adverse Events**

The investigator is responsible for collecting all adverse medical events that occur from the signing of the informed consent form to the end of the safety follow-up period (28 days  $\pm$  3 days after the last dose).

After the end of the safety follow-up period, AE will no longer be actively collected. If an SAE occurs and the investigator believes there is a reasonable causal relationship between the SAE and the study drug, the SAE should be reported to the sponsor according to the SAE reporting process.

AEs that have not fully recovered or stabilized by the end of the safety follow-up period (regardless of causality), follow-up must be conducted until recovery (to baseline or complete recovery), clinical stability is achieved, or a reasonable explanation is obtained.

AEs occurring between the informed consent form and first use of the drug may be recorded in

the CRF as medical history/accompanying diseases unless they meet one of the following criteria, in which they should be recorded as AEs: harm caused by any clinical laboratory examination procedures; AEs caused by discontinuation of the study protocol; AEs caused by drugs other than the study drug.

All AEs that occur during the safety follow-up period after the first administration of the drug must be recorded, including information such as the name, the start and end dates (and times) of the AE, severity, seriousness, the investigator's assessment of the relationship with the study drug, measures taken for the study drug in response to the AE, and outcome.

- If a patient dies, the cause or symptom leading to the death should be reported as the AE name. "Death" should be considered as an outcome of the AE. If the cause of death is unknown, "death of unknown cause" should be reported as the AE name.
- Events that clearly correspond to the progression of the tumor disease should not be recorded as AEs. However, if the investigator determines that the event is atypical, accelerated progression, or caused by the study drug, it should be recorded as an AE.
- Any death event caused by any reason during the safety follow-up period should be reported to the sponsor according to the SAE process.

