#### **9.4.6. Safety Analysis**

- Analysis based on SS;
- Summarize the number and percentage of Treatment-emergent Adverse event (TEAE)/treatment-related TEAE, SAEs/treatment-related SAEs, TEAE leading to discontinuation/treatment-related TEAE leading to discontinuation during the course of treatment;
- Summarize the number and percentage of TEAEs/treatment-related TEAEs, SAEs/treatment-related SAEs, TEAEs leading to discontinuation/treatment-related TEAEs leading to discontinuation, based on SOC/PT;
- Summarize the incidence and percentage of TEAEs/treatment-related TEAEs, SAEs/treatment-related SAEs, TEAEs leading to discontinuation/treatment-related TEAEs leading to discontinuation by SOC/PT and severity;
- Provide a detailed list of TEAEs/Treatment-related TEAEs categorized by SOC/PT and severity;
- Laboratory indicators: Provide a cross table for clinical judgment before and after medication, and conduct a descriptive and diachronic analysis of the measured values and changes from the baseline of laboratory test measures before and after medication. Provide a detailed list of examination results;
- Electrocardiogram: Provide a cross-tabulation of clinical judgments before and after medication, and perform descriptive and longitudinal analyses of the measured values and changes from baseline of electrocardiogram measures at each time point before and after medication. Provide a detailed list of the examination results;
- Physical examination: Provide a cross-tabulation of clinical assessments before and after medication, and provide a detailed list of examination results;

- Vital signs: Descriptive and longitudinal analyses will be performed on the measured values and changes from the baseline of various measures before and after medication. A detailed list of examination results before and after medication will also be provided.

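### The TEAE definition, the safety endpoint and the overview AE summary stop at treatment, while adverse events are recorded for a further 28 ± 3 days after the last dose

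*Protocol*

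**What the plan says.** **Definition.** Section 8.3.1.3 describes TEAEs as "Events that occur during treatment that are not present before treatment or have worsened compared to before treatment". No days after the last dose are added there or elsewhere.

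**Endpoint.** Section 3, and the synopsis in the same words, lists as a secondary endpoint "Treatment-emergent adverse events (TEAEs) and serious adverse events (SAEs) during the treatment period".

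**Analysis.** The overview bullet in section 9.4.6 covers TEAEs, SAEs and events leading to discontinuation. It ends with "TEAE leading to discontinuation/treatment-related TEAE leading to discontinuation during the course of treatment"; the synopsis version has an equivalent limit. Two further bullets, by SOC/PT and by SOC/PT and severity, repeat the same event types without a time limit. The AE listing is confined to TEAEs: "Provide a detailed list of TEAEs/Treatment-related TEAEs categorized by SOC/PT and severity".

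**Collection.** Section 8.3.7 has the investigator collect events "from the signing of the informed consent form to the end of the safety follow-up period", which it sets at 28 ± 3 days after the last dose. It adds: "All AEs that occur during the safety follow-up period after the first administration of the drug must be recorded". Any death in that period goes to the sponsor through the SAE process.

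**Schedule.** In section 1.2 the treatment period, the end-of-treatment visit and the "Safety Follow-up Period" are separate columns.

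**The concern.** The reporting window is shorter than the collection window, and the protocol itself names the difference as a separate period. Events in that period are recorded, but the definition and endpoint give them no place in the main safety results.

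This is a single-arm trial, so the absolute event rate is the safety result; no control arm is affected in the same way. The omission works in one direction only, because leaving out a period in which events are recorded can lower the reported rates but cannot raise them.

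The trial's only AE of special interest shows the effect. It is QT prolongation of CTCAE grade 3 or higher (section 8.3.8.3), and an ECG is scheduled at the safety follow-up visit. A non-serious prolongation first seen at that visit would enter the ECG summaries but would not count as a TEAE.

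**Working it through.** **Step 1: the windows side by side**

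| Item | Section | Start | End |
|---|---|---|---|
| AE collection | 8.3.7; 1.2 note 15 | Consent | 28 ± 3 days after last dose |
| TEAE definition | 8.3.1.3 | Treatment | End of treatment |
| TEAE and SAE endpoint | Synopsis; 3 | Treatment period | End of treatment period |
| Overview summary | Synopsis; 9.4.6 | Treatment | End of treatment |
| TEAE tables and listing | 9.4.6 | As TEAE definition | As TEAE definition |
| SAE tables by SOC/PT, and by severity | 9.4.6 | No limit stated | No limit stated |
| SAE definition | 8.3.1.4 | After receipt of study drug | No limit stated |

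**Step 2: where an event starting in safety follow-up is counted**

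- *Non-serious AE:* not a TEAE, so not in the endpoint, the overview, the SOC/PT tables or the AE listing. No table or listing of all collected AEs is planned.
- *SAE, including a fatal one:* outside the endpoint and the overview as worded. It meets the SAE definition and can enter the two SAE tables that carry no time limit. The endpoint and those tables could then count different events.
- *Death:* also enters overall survival (9.4.4) and, as a withdrawal reason under 7.2, the disposition summary (9.4.2).

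**Step 3: share of AE observation time affected**

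The protocol states no such share and no expected treatment duration, so this is an illustration. Inputs from the protocol: 21 dosing days and 7 drug-free days per 28-day cycle (6.1.2), and follow-up of 28 days, range 25 to 31 (8.3.7). Assumption: the last dose falls on day 21 of the final cycle. For c cycles:

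- Last dosing day: L = 28(c − 1) + 21, which is 49, 161 and 273 for c = 2, 6 and 10.
- Observation from first dose to the end of follow-up: L + 28 = 77, 189 and 301 days.

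Reading A counts the 7 drug-free days as treatment, because the day-28 visit sits in the treatment-period column. The affected part is 28 − 7 = 21 days. Reading B ends treatment at the last dose, so the affected part is 28 days.

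| Cycles | Reading A | Reading B |
|---|---|---|
| 2 | 21/77 = 27% | 28/77 = 36% |
| 6 | 21/189 = 11% | 28/189 = 15% |
| 10 | 21/301 = 7% | 28/301 = 9% |

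The ± 3 days move these figures modestly. For 2 cycles, reading A runs from 18/74 = 24% to 24/80 = 30%, and reading B from 25/74 = 34% to 31/80 = 39%.

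The share is largest for patients who stop early. It measures observation time; the protocol gives no event rates from which missed events could be estimated.

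**The case against.** **A reader might infer that post-treatment SAEs and deaths vanish from every planned table.** The documents do not support that. The SAE definition runs from receipt of study drug without an end date, and the two SAE tables by SOC/PT carry no time limit. Deaths also enter overall survival and disposition. The firm gap for SAEs and deaths is the endpoint wording and the overview.

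**A reader might also infer that the whole follow-up is wasted**, for instance as 83 × 28 = 2,324 patient-days of unused data. That figure would require every patient to stop treatment and complete follow-up, and it ignores reading A. Laboratory tests, ECG, vital signs and physical examination are scheduled at the safety follow-up visit, and section 9.4.6 analyses or lists their results. What is lost is the AE term, not every finding.

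**An exact TEAE cut-off often belongs to the SAP, and the end of treatment is never dated.** Both are fair observations, and the 21/7 schedule shows that treatment cannot mean dosing days alone. But the protocol is not silent: it limits the definition, the endpoint and the overview to treatment and gives follow-up its own period. Section 9 bases the SAP on the protocol's main features and expects consistency. A SAP with a 28-day window would depart from sections 3 and 8.3.1.3; one that followed them would leave recorded events out.

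**Few events may be involved.** Toxicity that led to stopping began on treatment and already counts. Events that clearly correspond to tumour progression are generally not recorded as AEs (8.3.7). This stands and limits the expected effect, but it does not remove the mismatch.

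**Conclusion.** The point holds in a limited form and should be corrected. On the literal text, non-serious AEs starting in safety follow-up reach no planned AE table or listing. SAEs and deaths in that window lie outside the stated endpoint and the overview, while the SAE tables by SOC/PT may include them.

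The part of AE observation time concerned is roughly 7% to 27% under reading A, or 9% to 36% under reading B, for 10 down to 2 cycles. These figures rest on assumed durations and on a last dose on day 21 of the final cycle. The effect on event rates cannot be quantified from the protocol; only its direction, downward, is clear. The primary endpoint, the sample size of 83 and the 34-response rule are unaffected.

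**What to change.** - In section 8.3.1.3, define a TEAE as an AE that starts or worsens from the first dose to the end of the safety follow-up period, 28 ± 3 days after the last dose.
- Use the same window for the TEAE and SAE endpoint in the synopsis and section 3.
- Apply it to all AE summaries and listings in section 9.4.6 and to the matching synopsis text. State that deaths in the window are included, so that the overview, the SOC/PT tables and the endpoint count the same events.

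The cost is wording only: section 8.3.7 already requires the data, and no visit or procedure changes. The downside is that reported event rates rise slightly.
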